| Health conditions       | Breast cancer screening                                                                                                                                                                                                                                                                                                                                                                                                                                                                                                                                  |
| Study design            | Randomized controlled interventional study with parallel assignment to 1 of 6 groups                                                                                                                                                                                                                                                                                                                                                                                                                                                                     |
| Interventions           | Group 1 – no message exposure;
Group 2 – single clinician message at Wave 1 on screening cessation; no message at Wave 2.                                                                                                                                                                                                                                                                                                                                                                                                                             |

|                       |                                                                                                                                                                                                                                                                                                                                                                                                                                                                                                                                          |

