|-----------------------|------------------------------------------------------------------------------------------------------------------------------------------------------------------------------------------------------------------------------------------------------------------------------------------------------------------------------------------------------------------------------------------------------------------------------------------------------------------------------------------------------------------------------------------|
|                       | Group 3 – message from news story at Wave 1 on screening cessation; message from clinician at Wave 2 on screening cessation.
Group 4 – message from family member at Wave 1 on screening cessation; message from clinician at Wave 2 on screening cessation.
Group 5 – message from news story at Wave 1 on screening continuation; message from clinician at Wave 2 on screening cessation.
Group 6 – message from family member at Wave 1 on screening continuation; message from clinician at Wave 2 on screening cessation. |
| Outcome measures      | Primary outcomes: support for stopping screening for a hypothetical older woman in the survey vignette
Secondary or other pre-specified outcomes: screening intention for participants; breast cancer screening attitudes; perceived message effectiveness; emotional response; negative perceptions of mammograms; awareness of screening harms; confusion or backlash about conflicting messages                                                                                                                                    |
| Eligibility           | Inclusion criteria: 65 years; female; part of an online survey panel called KnowledgePanel; able to complete survey in English.
Exclusion criteria: personal history of breast cancer                                                                                                                                                                                                                                                                                                                                                 |

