**C.4. Interventions and Choice of comparator:**

We will randomly assign women meeting eligibility to 6 groups (Table 1). The experimental groups 3-6 will read a message at Wave 1 that may be from either family/friend or the media followed by a second message from a clinician one to two weeks later at Wave 2, as research suggests that message decay occurs in 1-2 weeks. By presenting the non-clinician message first, we aim to mimic the real-world scenario where patients are often exposed to information from their family, friends and/or the media before a clinic visit.

The clinician message will be directed at reducing over-screening, mentioning the harms of over-screening and supporting screening cessation. We will systematically vary the non-

clinician message to be either consistent with the clinician message (also mentions harms of over-screening and supports screening cessation) or conflicting (mentions benefits of screening, supports continued screening and opposes screening cessation). We include a no-exposure control group (Group 1) where the participants read no message at either time point. We also include a single exposure group that reads only the clinician message (Group 2).

Table 1. Aim 2 experimental design

| Group # | Group type                | Wave 1        |                    | Wave 2     |                |
|---------|---------------------------|---------------|--------------------|------------|----------------|
|         |                           | Source        | Content            | Source     | Content        |
| 1       | Control (no exposure)     | No message    | No message         | No message | No message     |
| 2       | Control (single exposure) | Clinician     | Stop screening     | No message | No message     |
| 3       | Experimental              | Media         | Stop screening     | Clinician  | Stop screening |
| 4       | Experimental              | Family/Friend | Stop screening     | Clinician  | Stop screening |
| 5       | Experimental              | Media         | Continue screening | Clinician  | Stop screening |
| 6       | Experimental              | Family/Friend | Continue screening | Clinician  | Stop screening |

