#### **C.6. Statistical methods and sample size.**

The main analysis focuses on the primary outcome assessed at Wave 2 with the independent variables being the randomly assigned message/messenger combinations. The primary goal is to compare the experimental groups (Groups 3-6) at Wave 2 with both control groups to assess the combined effect of consistent and conflicting messages over time. We hypothesize that the participants who read consistent messages both directed at reducing over-screening (Groups 3,4) will have higher support and higher intentions to stop screening than participants who read clinician message alone (Group 2); the participants who read conflicting messages (Groups 5,6) will have lower intentions to stop screening than participants who read clinician message alone (Group 2). We will compare the mean scores across groups using ANOVA and adjust for multiple comparisons. We will conduct exploratory analyses by key covariates, including age, predicted life expectancy based on health and functional status, to examine the impact of messaging within these subgroups.

Power calculations are based on preliminary data in which we asked 41 patients 65+ about willingness to stop routine cancer screening if recommended by their clinician. Based on the distribution of responses from this preliminary data, we estimate that with 400 participants randomized to each group at Wave 2, we will have 80% power to detect a 0.30 point difference for the primary outcome. The survey company Ipsos that manages and maintains the KnowledgePanel affirms that, through their recruiting strategy and based on their past experience, 20% attrition or less is expected between the two waves over 1-2 weeks. Assuming 20% attrition, we will target 500 per group at Wave 1.

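### At Wave 2, Group 2's clinician message is one to two weeks old while Groups 3-6 have just read theirs, so every contrast with Group 2 mixes the pairing effect with message decay

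*Protocol*

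**What the plan says.** The registration table (section A) describes the clinician-only arm as "Group 2 – single clinician message at Wave 1 on screening cessation; no message at Wave 2". Table 1 in C.4 agrees, so this is not a misprint. The experimental arms have the reverse timing, for example "Group 3 – message from news story at Wave 1 on screening cessation; message from clinician at Wave 2 on screening cessation". C.4 describes Groups 3-6 as reading a non-clinician message "followed by a second message from a clinician one to two weeks later at Wave 2", and justifies the gap "as research suggests that message decay occurs in 1-2 weeks".

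C.6 then fixes the time point: "The main analysis focuses on the primary outcome assessed at Wave 2". It fixes the comparators: "The primary goal is to compare the experimental groups (Groups 3-6) at Wave 2 with both control groups". For Groups 3 and 4 the hypothesis is "higher support and higher intentions to stop screening than participants who read clinician message alone (Group 2". For Groups 5 and 6 it is lower intentions to stop than in the same Group 2. C.6 plans ANOVA with an adjustment for multiple comparisons. It does not mention that Group 2 and Groups 3-6 differ in how recently they read the clinician message.

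Table 2 in C.5 collects the primary outcome in every group at both waves.

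**The concern.** The aim in section B is to learn whether a second source strengthens or weakens the effect of the clinician's message. That requires the clinician message to be held constant while the other message varies. Against Group 2 at Wave 2 it is not constant: one side has just read it, and the other read it one to two weeks before. No arm reads only the clinician message at Wave 2.

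The resulting shift has the same sign in both hypotheses. It raises Groups 3,4 relative to Group 2, so strengthening can appear when the first message added nothing. It also raises Groups 5,6 relative to Group 2, so a real weakening can be masked. Neither a larger sample nor a multiplicity adjustment removes a shift of this kind.

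**Working it through.** **Inputs from C.6:** 400 per group at Wave 2, 80% power, 0.30-point difference, 20% attrition, 500 per group at Wave 1. **Not given:** SD, alpha, E, f. Two-sided 0.05 is assumed. E and f are varied.

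**1. The plan's own figures.** 500 × 0.8 = 400 per group, and 6 × 500 = 3000, as stated. The power figure cannot be reproduced without an SD, so the SD is back-solved: 0.30 / ((1.96 + 0.842) × √(2/400)) = 1.514. The standard error of a pairwise difference is then 1.514 × √(2/400) = 0.107. If a Bonferroni correction over eight contrasts (four experimental groups by two controls) were already built in, the implied SD would be 1.19 instead.

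**2. What each contrast estimates.** Let D be what the first message adds at Wave 2 in group g, and take Group 1 as zero.

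- Group g at Wave 2: E + D
- Group 2 at Wave 2: f × E
- Group g minus Group 2: D + (1-f)E, so shifted by (1-f)E
- Group g minus Group 1: E + D, the total effect of both messages, with no shift
- Groups 3,4 minus Groups 5,6: the difference between their D values, because E cancels; no shift

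**3. Size over a range.** False strengthening (true D = 0) = Φ(shift/0.107 - 1.96). Power for a true D of -0.30 = Φ((0.30 - shift)/0.107 - 1.96).

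| Shift | Example | False strengthening | Power for -0.30 |
|---|---|---|---|
| 0 | f = 1 | 2.5% | 80% |
| 0.075 | E 0.30, f 0.75 | 10% | 56% |
| 0.15 | E 0.30, f 0.5 | 29% | 29% |
| 0.20 | E 0.40, f 0.5 | 46% | 15% |
| 0.30 | E 0.60, f 0.5 | 80% | 2.5% |

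**4. With a multiplicity adjustment.** Bonferroni over eight contrasts at the same SD gives false strengthening of about 9%, 19% and 53% at shifts of 0.15, 0.20 and 0.30. Power for -0.30 with no shift is then about 53%, not 80%. The rates fall but the shift remains.

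**5. Cross-wave contrast.** (Group g minus Group 1 at Wave 2) minus (Group 2 minus Group 1 at Wave 1) estimates (E + D) - E = D. With an assumed between-wave correlation of 0.6, the Group 1 part contributes 2 × (1 - 0.6)/400 = 0.8/400. In units of SD², the variance is 1/400 + 1/500 + 0.8/400 = 0.0065 if all 500 of Group 2 are used at Wave 1, or 2.8/400 = 0.0070 with 400. The simple contrast has 2/400 = 0.0050. The detectable difference becomes 0.30 × √1.3 = 0.34 to 0.30 × √1.4 = 0.36.

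**6. Groups 3,4 versus 5,6 pooled.** With 800 a side, the detectable difference is 0.30/√2 = 0.21 on the same assumptions.

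**The case against.** C.6 names both control groups and speaks of combined effects over time, so the Group 2 contrast could be meant as a durability reference. The first part of this stands: the Group 1 contrasts answer the combined-effect question and Group 2's timing does not touch them. The durability reading does not fit the hypotheses, which concern consistent and conflicting pairing.

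The two hypotheses are not equally exposed. For Groups 5,6 the shift runs against the hypothesis, so a significant weakening would hold despite it, provided the clinician message raises support and fades rather than grows. Only a null or opposite result there is uninterpretable. This stands.

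The rates in the table are conditional. C.4 says decay occurs but not how much, and the planned test is adjusted for multiplicity in a way that C.6 does not specify. For Groups 5,6, C.6 names only intentions, and a participant's own screening intention is a secondary outcome. The power column therefore carries the primary outcome's 0.30 and SD over to that hypothesis. All of this stands, and the figures are illustrations.

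A reader might infer that the trial cannot answer its primary question. The documents do not support that: Groups 3-6 are balanced on clinician-message timing, and the Group 1 contrasts are clean. What neither can show is whether a paired arm differs from the clinician message alone, which is what both hypotheses assert.

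**Conclusion.** The point holds for the Wave 2 contrasts with Group 2, and only for those. They estimate the pairing effect plus (1-f)E. The direction follows from the protocol's own statement on decay, if the clinician message has a positive effect. The size cannot be fixed from the document. On the assumptions shown, a shift of 0.15 points, half the difference the trial is powered for, gives about 29% false strengthening unadjusted (9% with Bonferroni over eight) and reduces unadjusted power for a -0.30 effect to 29%. With no decay (f = 1) there is no bias, but that would contradict C.4.

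A reader might take 46% or 80% as the expected false-positive rate. Those values belong to shifts of 0.20 and 0.30 and to an unadjusted test, and nothing in the protocol says such shifts are likely.

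**What to change.** **Before fielding:** give Group 2 no message at Wave 1 and the clinician message at Wave 2, so that every clinician message is read just before the Wave 2 outcome. This means reprogramming one arm, with no added participants. The durability estimate and the Wave 1 clinician-only reading are lost. The registration table lists a study start of May 12, 2023 and completion of June 19, 2023, so this option may no longer be open.

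**If the arms stay as they are,** change C.6 as follows:

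1. Make Groups 3,4 versus Groups 5,6 at Wave 2 the confirmatory test of consistent versus conflicting pairing. It needs no new data and is free of the shift. It does not show whether either pairing differs from the clinician message alone.
2. State that the Group 2 contrast at Wave 2 includes decay of the clinician message and is not a pure pairing effect. State also that a null or opposite result for Groups 5,6 against Group 2 cannot be read as absence of weakening.
3. Report (Group g minus Group 1 at Wave 2) minus (Group 2 minus Group 1 at Wave 1) as a supporting analysis. Name its assumptions: the immediate clinician effect is the same at either wave, wave and repeat-measurement effects are additive, and attrition is similar across arms. These make it unsuitable as the sole confirmatory contrast. Its precision cost is a detectable difference of about 0.34 to 0.36 instead of 0.30, if the between-wave correlation is 0.6.

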**C.3. Eligibility Criteria**

- Inclusion criteria: 65 years; female; part of KnowledgePanel; able to complete survey in English.
- Exclusion criteria: personal history of breast cancer

KnowledgePanel already collects information on panel members' age, gender, English proficiency. We will independently include a screening question at the beginning of the survey regarding breast cancer history.

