Support for screening cessation for hypothetical patient: “How strongly do you believe that older women with a lot of health problems like [name] should get a mammogram in the next two years? Measured on a 7-point scale (1=definitely should get a mammogram; 7= definitely should not get a mammogram).

Screening intention for oneself: “How likely is it that you will get a mammogram in the next two years?” Measured on a 7-point scale (1=very likely to get a mammogram, 7=very unlikely to get a mammogram).

Attitudes:

- “For you, would you say getting a mammogram in the next two years is... 1=unimportant; 5=important; 1=harmful; 5=beneficial; 1=not worthwhile; 5=worthwhile;

- “For older women with a lot of health problems like [name], would you say getting a mammogram in the next two years is... 1=unimportant; 5=important; 1=harmful; 5=beneficial; 1=not worthwhile; 5=worthwhile;

Awareness of harms of screening: “Have you ever heard or read the following information? You could have heard or read this information during this survey or previously.” (Yes/No)

- For some women over age 65 who have a lot of health problems, medical guidelines recommend against regular mammograms.
- Mammograms can find slow-growing breast cancers that might never cause problems but can lead to unnecessary, risky treatments such as surgery or radiation.
- Mammograms can have false alarm results that may cause stress, anxiety, and require breast biopsy.

Negative perceptions of mammograms:

“Thinking about the information that was shared, please rate how much you agree or disagree with the following statement.” (1=strongly disagree; 5=strongly agree)

- This information discourages me from wanting to get a mammogram.
- This information makes getting a mammogram seem unpleasant to me.
- This information makes me concerned about the health effects of getting a mammogram.

Effect perceptions:

“Thinking about the information that was shared, please rate how much you agree or disagree with the following statement.” (1=strongly disagree; 5=strongly agree)

- This information would make me think carefully about getting a mammogram
- This information would make me want to find out more information about the potential benefits of getting a mammogram.
- This information would make me want to find out more information about the potential downsides of getting a mammogram.

Emotional response:

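### The primary Wave 2 comparison is a plain ANOVA, although age and the allocation sort variables are on file before randomisation: a valid analysis that could be made slightly more efficient (minor)

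*Protocol*

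**What the plan says.** Protocol C.6 places the main analysis on the primary outcome at Wave 2, with "the independent variables being the randomly assigned message/messenger combinations". The method is then given: "We will compare the mean scores across groups using ANOVA and adjust for multiple comparisons". No baseline covariate is named in that model.

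The next sentence of C.6 turns to other variables: "We will conduct exploratory analyses by key covariates, including age, predicted life expectancy based on health and functional status". Their stated purpose is to look at message effects within subgroups.

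Four baseline variables are available before any message is read:

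- **Age.** C.3 says "KnowledgePanel already collects information on panel" members' age.
- **Race/ethnicity, geographic region and education.** C.2 sorts participants on these before sequential allocation to the six groups, and notes that the panel already has them.

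The primary item (C.5) asks about a hypothetical older woman with many health problems: "Measured on a 7-point scale (1=definitely should get a mammogram; 7= definitely should not get a mammogram".

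The sample-size statement in C.6 is that "with 400 participants randomized to each group at Wave 2, we will have 80% power" for a difference of 0.30 points. It states no SD, alpha or number of comparisons.

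**The concern.** In a linear model, any part of the outcome that a pre-randomisation variable predicts can be removed from the error term at the cost of one degree of freedom per coefficient. With 6 × 400 = 2,400 completers that cost is negligible. The design states 80% power and no margin above it. It also has no pre-message outcome score that could serve as a covariate: Table 1 gives Groups 2 to 6 a message at Wave 1, and Table 2 lists no assessment before it. The panel variables are therefore the main documented candidates.

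Two features of the allocation matter. Age is not a sort variable, so its balance across groups is left to chance. Race/ethnicity, region and education are sort variables, and where allocation balances a prognostic factor, an analysis that ignores the factor tends to overstate the standard error. Including those factors brings the analysis into line with the allocation.

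What is at stake is some precision in the primary contrasts. The validity of the comparison is not in question.

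**Working it through.** **Inputs from the protocol (C.6):** 400 per group at Wave 2; 80% power; difference 0.30 points; 20% attrition; 500 per group at Wave 1.

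**Assumptions:** two-sided alpha 0.05 with one comparison as the base case, and 4, 8 or 15 Bonferroni comparisons as a range (15 is all pairs of six groups). R-squared is taken as 2%, 5% and 10%; the documents give no value.

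**Step 1. The plan's own figures.** 400 / (1 − 0.20) = 500 per group, and 6 × 500 = 3,000, which agrees with the total in section B. The 80% power cannot be reproduced independently because no SD is given, so the SD is back-solved:

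SD = 0.30 / [(z for 1 − alpha/2 + z for 0.80) × √(2/400)] = 0.30 / [(1.960 + 0.842) × 0.0707] = **1.514**.

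With 4, 8 and 15 comparisons the implied SD is 1.271, 1.186 and 1.123.

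**Step 2. Effect of adjustment.** The residual SD becomes SD × √(1 − R²). The detectable difference becomes 0.300 × √(1 − R²), and the equivalent unadjusted sample size is 400 / (1 − R²). Power is Φ(2.802 / √(1 − R²) − 1.960) in the base case. For R² = 5%: √0.95 = 0.975, 2.802 / 0.975 = 2.874, 2.874 − 1.960 = 0.914, and Φ(0.914) = 0.820.

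| R² | Detectable difference | Equivalent n per group | Power, 1 comparison | Power, 4 | Power, 8 | Power, 15 |
|---|---|---|---|---|---|---|
| 0 | 0.300 | 400 | 80.0% | 80.0% | 80.0% | 80.0% |
| 2% | 0.297 | 408 | 80.8% | 80.9% | 81.0% | 81.1% |
| 5% | 0.292 | 421 | 82.0% | 82.3% | 82.5% | 82.6% |
| 10% | 0.285 | 444 | 84.0% | 84.7% | 85.0% | 85.2% |

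The number of comparisons hardly changes the gain; R² determines it.

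**Step 3. Size of chance imbalance.** With 400 per group, the standardised difference in a covariate between two groups has standard error √(2/400) = 0.071. At R² = 5% the correlation with the outcome is √0.05 = 0.224. One standard error of imbalance then moves a contrast by 0.071 × 0.224 × 1.514 = 0.024 points, against a target of 0.30.

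**Step 4. Cost of missing covariate values.** If completers with a missing covariate (fraction m) are dropped, the effective n is 400 × (1 − m) / (1 − R²). This falls back to 400 when m = R². At R² = 5%, 5% missing values cancel the gain.

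**The case against.** The strongest reply is that nothing here is wrong. An ANOVA of randomised groups is unbiased, and using variables for exploratory subgroups does not oblige anyone to put them in the primary model. Covariate choice is also often left to the statistical analysis plan, which was not available for this review. The first part stands, and it is why this is an efficiency point only. The second part carries less weight, because C.6 does name the independent variables and the method, so the unadjusted model is a stated choice.

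Three stronger readings are tempting, and the documents do not support them:

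- **A reader might infer that material precision is being lost.** The primary item concerns a fixed hypothetical woman. Nothing in the protocol says that a respondent's own age or background predicts her view of that woman. The link may be closer for her own screening intention, but that is a secondary outcome and no figure is given for it either.
- **A reader might infer that predicted life expectancy is an equally costless covariate.** It rests on health and functional status items whose timing relative to the Wave 1 message is not stated. Section D.2 lets participants skip questions, so the score may also be incomplete, with the effect shown in step 4.
- **A reader might infer that chance imbalance on age distorts the comparison.** Such imbalance is already reflected in the ANOVA standard error. It is not a bias, and step 3 shows that its typical size is small.

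**Conclusion.** The point holds as a minor efficiency improvement. C.6 specifies an unadjusted primary comparison while age and the three sort variables are on file before randomisation and cannot be affected by the messages.

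The base-case gain is 0.8, 2.0 and 4.0 power points at R-squared of 2%, 5% and 10%. That assumes two-sided alpha 0.05, one comparison and the SD of 1.514 back-solved from the plan's own power statement. The true R-squared is unknown. For a vignette item the low end, 2 power points or less, is the more reasonable expectation. The unadjusted ANOVA remains valid, and conclusions drawn from it would not be wrong on this account.

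**What to change.** Amend C.6, and the statistical analysis plan to match:

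- Prespecify the primary model as a linear model for the Wave 2 outcome with group, continuous age, race/ethnicity, region and education.
- Base the multiplicity-adjusted contrasts on the adjusted means, and report the unadjusted ANOVA as a sensitivity analysis.
- Add the predicted life-expectancy score only if its items are collected before the Wave 1 message.
- State a simple rule for missing covariate values so that no completer is dropped.
- State that Wave 1 outcome scores are not used as covariates, because in Groups 2 to 6 they are measured after exposure.

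The cost is a few sentences and one degree of freedom per added coefficient out of roughly 2,400. The panel variables need no new data collection. Fixing the model in advance also removes any later choice between adjusted and unadjusted results.
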